### 2.3 Planned sample size

In order to devise the sample size, we conducted an estimated power analysis to establish the size of the groups (75 patients in each group) and strive for 80% power. Hence, the maximum estimated number of participants is 600.

The sample comprises consecutive migraine patients who meet the inclusion criteria and visit a neurologist in a partner clinic. In section 2.5, the precise involvement of patients is outlined.

Consent to participate in the research is voluntary and does not affect the patient’s ability to use the Migrevention solution or their usual minimal treatment options.

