### 2.8 Settings and randomization process

The study will be conducted in parallel for each intervention setting—the four study groups (digital treatment groups) and the four control groups (standard interdisciplinary treatment groups or treatment standard groups) (Table 3).

**Table 3 pdig.0000295.t003:** Division of groups.

Study group I	Control group I	Study group II	Control group II	Study group III	Control group III	Study group IV	Control group IV
UMT^1^	UMT	UMT	UMT	UMT	UMT	UMT	UMT
DHD^2^	PD^3^	DHD	PD	DHD	PD	DHD	PD
		DHN^4^	UHN^5^	DHN	UHN	DHN	UHN
				dCBT^6^	uCBT^7^	dCBT	uCBT
						dPT	uPT

^1^UMT–Usual Minimal Treatment

^2^DHD–Digital Headache Diary

^3^PD–Paper Diary

^4^DHN–Digital Treatment by Headache Nurse

^5^UHN–Usual Treatment by Headache Nurse

^6^dCBT–Digital CBT Programme

^7^uCBT–Usual CBT Programme

^8^dPT—Digital Physiotherapy

^9^uPT–Usual Physiotherapy

After the initial informed consent, patients who qualify for the study will be added to the research group and assigned a participation number based on the precise time the study group acquired the contact information of the patient (date and time, if necessary). After the informed consent is signed, participants are randomized into eight groups. A randomization table has been created for this purpose, in which 600 distinct numbers are randomly separated into eight groups. The patient is assigned to a group in accordance with the randomization table.

All groups receive the usual minimal treatment consisting of medications in addition to the usual appointment with a neurologist. Control groups receive the usual treatment consisting of medications, the usual appointment with a neurologist, headache nurse, CBT therapist and a physiotherapist, in different combinations. All ‘as usual’ treatments involve clinical face-to-face contact.

All participants of the study groups receive digital treatment consisting of medications and a neurologist appointment as usual. Additionally, each participant is assigned digital appointments with the following specialists: headache nurse, CBT therapist and/or physiotherapist. These appointments are assigned in different combinations depending on the randomization. The digital interventions are delivered through the Migrevention Clinical solution.

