## 3. Discussion

Designed by an interdisciplinary team, our research aims to compare digitally mediated NI migraine treatment options with conventional ones, determine the optimal approach for enhancing patient health and quality of life, optimizing specialists’ time, and extending assistance to more migraine patients.

A notable strength of this study is its status as a prospective randomized controlled study of a novel, standardized, manual-based intervention that focuses on, among other things, monitoring compliance and compares fully digital intervention with conventional interdisciplinary NI. Another strength of the study is the assessment of the efficacy and applicability of each treatment component separately, in addition to the whole treatment protocol.

The authors hope that the study helps to overcome the challenges in the field of digital therapeutics (DTx) [62]. The study provides an opportunity to begin to determine the effectiveness of DTx in the treatment of migraine. The implementation of the project also contributes to the integration of DHD data with the e-health system so that they are usable for all providers (including general practitioners) as well as the connection of DHDs to electronic health records.

Interdisciplinary intervention in migraine treatment is known to be effective, especially in preventing migraine chronification [63]. Given the high risk of migraine chronification, long-term treatment adherence and follow-up may be essential to ensure the long-term effectiveness of digital interventions [64]. Based on the above, the research plans to conduct long-term follow-up studies (3, 6, 9 months after the end of the intervention).

There are some limitations that may affect the conduct and results of the study and must be considered when interpreting the results in the future.

The initial sample size will see at least 75 patients in each group, according to the Power analysis. Due to the time-consuming conventional interventions and the time needed to collect data, the realistic obtainable group size within the given timeframes of the study may be smaller. The study may favour the larger clinics and research centers for adopting the protocol and conducting the study and limit similar possibilities of smaller centers. In order to overcome this problem, interim analyses can be undertaken to examine statistically significant associations in a smaller number of patients.

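### Interim significance tests in fewer patients cannot make up for groups smaller than 75, and repeated unadjusted looks would raise the type I error

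*Protocol article*

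**What the plan says.** Section 2.3 of the protocol article reports a power analysis done "to establish the size of the groups (75 patients in each group) and strive for 80% power", and concludes that "the maximum estimated number of participants is 600". Section 2.8 allocates these patients to eight groups, four digital and four conventional, which form four digital/control pairs.

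Section 3, among the limitations, restates the target: "The initial sample size will see at least 75 patients in each group, according to the Power analysis". It then concedes that, because conventional treatment and data collection take time, "the realistic obtainable group size within the given timeframes of the study may be smaller". After one sentence on larger and smaller centres it gives the remedy, introduced as the means of overcoming the problem: "interim analyses can be undertaken to examine statistically significant associations in a smaller number of patients".

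Section 2.11 names software and model families and mentions no interim analysis. The article gives no alpha, target difference or standard deviation.

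**The concern.** The sentence has the role of an interim analysis the wrong way round. A trial that expects too few patients has a power problem. Testing a subset of those patients for significance uses even less information, so it cannot solve that problem. What it can do is add further occasions on which a chance difference crosses the threshold.

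Two things are at stake. First, a reader or the study team may treat a significant result in a small subset as making up for the missing patients. Such results overstate the effect on average. Second, if the same comparison is tested more than once at an unadjusted level, the stated error rate no longer holds. The trial is open-label (section 2.2), its primary outcome comes from patient diaries (section 2.5), and section 2.2 describes real-time monitoring of data in the digital format, so informal looks would be easy to make.

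**Working it through.** **Inputs from the article:** 75 per group, 80% power, 8 groups, maximum 600 (sections 2.3 and 2.8).

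**Assumptions, because the article does not give them:** two-sided alpha of 5%, comparison of two means within one digital/control pair, normal approximation, equally spaced looks.

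**1. The plan's own figure.** 8 × 75 = 600, which agrees. The link from 75 per group to 80% power cannot be reproduced without an effect size, standard deviation and alpha. It can be solved backwards for the standardised difference d:

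d = (1.960 + 0.842) × √(2/75) = 2.802 × 0.1633 = 0.457.

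**2. Power for that effect in smaller groups.** Power = Φ(d × √(n/2) − 1.960).

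- n = 75: Φ(2.802 − 1.960) = Φ(0.842) = 80%
- n = 60: Φ(2.506 − 1.960) = Φ(0.546) = 71%
- n = 50: Φ(2.287 − 1.960) = Φ(0.327) = 63%
- n = 37: Φ(1.968 − 1.960) = Φ(0.008) = 50%

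The 95% confidence interval half-width, 1.96 × √(2/n) in standard deviation units, grows from 0.32 at 75 to 0.39 at 50 and 0.46 at 37.

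**3. Type I error when one comparison is tested repeatedly at 5%.** Under no effect, the statistic at look k is Z(k) = (X1 + … + Xk)/√k with independent standard normal increments. The error is the probability that any |Z(k)| exceeds 1.96 (1,000,000 simulated trials).

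| Unadjusted looks | Type I error, one comparison |
|---|---|
| 1 | 5.0% |
| 2 | 8.3% |
| 3 | 10.7% |
| 4 | 12.6% |
| 5 | 14.2% |

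**4. Overstatement among significant results.** With a true d of 0.457, the mean absolute estimate among significant results, divided by the true value, is about 1.40 at 37–38 per group, 1.26 at 50 and 1.13 at 75.

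**5. One look at half the data plus a final analysis at the full 75 per group.**

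| Limits for \|z\| (interim / final) | Type I error | Power |
|---|---|---|
| 1.96 / 1.96, unadjusted | 8.3% | 82.0% |
| 2.178 / 2.178, Pocock | 5.0% | 75.6% |
| 2.797 / 1.977, O'Brien-Fleming | 5.0% | 79.7% |

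The O'Brien-Fleming limits correspond to about p<0.005 and p<0.048. Steps 2 and 5 together show that a boundary controls alpha at little cost when recruitment is complete. It does not recover the power lost when recruitment ends below 75 per group.

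**The case against.** The strongest reply is that this is one permissive sentence among the limitations of a condensed article. The analysis section plans no interim look, and looks, boundaries and alpha adjustment belong in an analysis plan that is not shown. That stands as far as it goes: the absence of a boundary is no finding. What remains is the stated reasoning that interim testing overcomes a small sample, and no analysis plan could make that true.

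It can also be said that the sentence directly before the remedy concerns larger and smaller centres, so the problem referred to is ambiguous. The reference to fewer patients ties it to the shortfall. On the other reading, testing fewer patients would not help small centres either.

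Several stronger readings are tempting and are not supported:

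- **That interim looks lower power.** They do not. Power falls because n is smaller. An unadjusted half-way look followed by a full final analysis rejects slightly more often (82.0% against 80%), and O'Brien-Fleming limits cost about 0.3 points.
- **That the trial's error rate is already inflated.** Inflation needs more than one unadjusted test of the same comparison. A single analysis at a smaller final n, which the wording also permits, leaves alpha where it was.
- **That early stopping, early publication or disclosure of comparative results to the treating team is planned.** The article describes none of these.
- **That the risk of a false positive is far higher because there are four digital/control pairs.** With one look and four independent tests at 5%, the chance of at least one is already 1 − 0.95⁴ = 18.5%. That is a separate multiplicity question, and the article does not say that any one significant pair would count as success.

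**Conclusion.** The point holds in a limited form. Section 3 presents interim significance testing in fewer patients as the way round group sizes below 75, and it cannot serve that purpose. For the effect implied by 75 per group and 80% power, power is about 63% at 50 per group and 50% at 37. Repeated unadjusted testing would raise the type I error of one comparison from 5% to between 8.3% (two looks) and 14.2% (five). Significant results at about half the planned size would overstate the effect by about 40% on average.

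These figures rest on an assumed two-sided 5% level, a back-solved effect of d = 0.457 and equally spaced looks. They show the size of the problem if the sentence is acted on. They do not describe what the trial has committed to. Since the sentence is permissive and no look is planned, this should be fixed, but it does not invalidate the design.

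**What to change.** Delete or reword the sentence in section 3 so that interim testing is not presented as a remedy for under-recruitment. Add to section 2.11 that outcomes are compared between groups once, when the last randomised patient reaches the primary time point (three months after the end of the intervention). State that any shortfall will be reported as reduced power, with the estimate and its wider confidence interval.

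If an earlier look is wanted, there are two acceptable forms:

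- limit it to feasibility data pooled over groups, such as recruitment, diary completion and the pooled standard deviation; or
- pre-specify a single comparative look with alpha control, for example O'Brien-Fleming limits of about p<0.005 at half the data and p<0.048 at the end, at a cost of about 0.3 points of power with full recruitment.

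This control applies to each comparison; multiplicity across the four pairs would need its own rule.

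The cost is about one sentence in each of the two sections. The team gives up unadjusted early comparative results.

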## Abstract

Migraine is one of the most frequent and expensive neurological disease in the world. Non-pharmacological and digitally administered treatment options have long been used in the treatment of chronic pain and mental illness. Digital solutions increase the patients’ possibilities of receiving evidence-based treatment even when conventional treatment options are limited. The main goal of the study is to assess the efficacy of interdisciplinary digital interventions compared to conventional treatment. The maximum number of participants in this multi-centre, open-label, prospective, randomized study is 600, divided into eight treatment groups. The participants will take part in either a conventional or a digital intervention, performing various tests and interdisciplinary tasks. The primary outcome is expected to be a reduction in the number of headache days. We also undertake to measure various other headache-related burdens as a secondary outcome. The sample size, digital interventions not conducted via video calls, the lack of human connection, limited intervention program, and the conducting of studies only in digitally sophisticated countries are all significant limitations. However, we believe that digitally mediated treatment options are at least as effective as traditional treatment options while also allowing for a significantly higher patient throughput. The future of chronic disease treatment is remote monitoring and high-quality digitally mediated interventions.The study is approved by the Ethics Committee of the University of Tartu for Human Research (Permission No. 315T-17, 10.08.2020) and is registered at ClinicalTrials.gov: NTC05458817 (14.07.2022).

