Limited studies have explored virtually mediated nurse counselling and digital physiotherapy. While a virtual nurse (avatar) may address healthcare challenges, it cannot diagnose or collaborate with other team members [40]. Online chatroom counselling with nurses offers opportunities to enhance clinical contact in digitally mediated interventions, but various limitations and challenges need addressing [49]. To our knowledge, the efficacy of digital physiotherapy in interdisciplinary headache treatments remains unstudied. A global shortage of headache specialists, including clinical psychologists, CBT therapists, physiotherapists, and headache nurses, contributes to long waiting lists and limited availability. Geographic constraints further impede access to services, particularly for those residing far from large centers. Digital NI options address these challenges by expanding access to services, utilizing professional intervention methods, reducing dropout rates, and thereby improving intervention efficacy [50,51].

The main goal of the present study is to assess the efficacy of interdisciplinary digital interventions compared to conventional treatment options.

The essential secondary objectives encompass evaluating individual and combined components of interventions, including adherence, credibility, clinical contact, and cost-effectiveness in comparison to conventional format.

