### 2.5 Primary outcome measure

The primary outcome measure is a reduction in the number of headache days (data derived from diaries) three months after the end of the interdisciplinary intervention programmes compared to the baseline (at the start of intervention).

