### 2.11 Statistical analysis

The programs SPSS and R will be used for data analysis. The use of the main generalized linear models for data analysis, such as ANOVA, MANOVA and multinomial linear regression analysis, is planned.

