Digital interventions, which are not conducted via video call, are unique strategies that may not be the preference of many individuals in certain situations. In digital interventions, the authors have planned patient initiated clinical contact only via chatroom. Studies on whether and how much clinical contact is required are controversial [14, 65]. The lack of human connection may affect patient adherence, increase the drop-out rate and limit treatment efficacy for some patients. The predetermined and limited number of techniques for use by the specialists may affect the flexibility of treatment. It must also be considered that the entire intervention programme is a minimum programme, and minimal intervention may not have sufficient power to prove the effectiveness of NI migraine treatment.

The whole intervention being done on Estonian patients is a limitation by itself. Estonia is a digitally advanced country whose residents use digital solutions daily. These settings may not be equivalent in other countries and cultures. Hence, the developed methodology is best applicable in countries with similar settings and consequently must be repeated in other countries with different settings.

The authors intend to demonstrate that digitally mediated treatment is at least as effective as conventional treatment but allows for a significantly higher patient throughput, saves/improves specialist workload and is cost-effective. The authors expect remote monitoring and high-quality digitally mediated interventions to be the future of chronic disease treatment.

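### The aim is to show that digital care is no worse than conventional care, but no margin or decision rule is stated, so short of superiority the trial as written cannot support it

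*Protocol article*

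**What the plan says.** The intended conclusion appears in section 3 (Discussion): "The authors intend to demonstrate that digitally mediated treatment is at least as effective as conventional treatment". The Abstract gives it as a belief: "we believe that digitally mediated treatment options are at least as effective as traditional treatment options". The formal goal at the end of section 1 is neutral: "The main goal of the present study is to assess the efficacy of interdisciplinary digital interventions compared to conventional treatment options". No section names a hypothesis type.

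On the primary outcome, section 2.5 states: "The primary outcome measure is a reduction in the number of headache days (data derived from diaries) three months after the end" of the programmes, compared with baseline.

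On analysis, section 2.11 states: "The use of the main generalized linear models for data analysis, such as ANOVA, MANOVA and multinomial linear regression analysis, is planned". It gives no margin and no rule based on a confidence limit, and neither does any other section.

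On size, section 2.3 reports a power analysis "to establish the size of the groups (75 patients in each group) and strive for 80% power", for a maximum of 600 in eight groups. It does not say which hypothesis, contrast or effect the power refers to. Section 3 adds that the groups may turn out smaller than 75, and that interim analyses could then look for statistically significant associations in fewer patients.

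**The concern.** A claim that one active format is no worse than another needs evidence that any deficit is smaller than a stated amount. A test of no difference supplies that only if it comes out significantly in favour of digital. If it is non-significant, the data may be compatible with equality, with a small deficit or with a deficit that matters, and the p-value does not separate these.

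The incentive also runs the wrong way. Smaller groups make non-significance more likely, and section 3 expects that the groups may be smaller. The trial's central conclusion could then rest on a lack of precision. Because a margin drives sample size, the gap also means that nothing shows whether 75 per group is enough for the stated aim.

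**Working it through.** **Inputs from the article.** Eight groups, 75 per group, 80% power (section 2.3); four digital-versus-conventional pairs (section 2.8, Table 3).

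**Assumed, because the article gives none.** Two-sided 5% level (one-sided 2.5% for non-inferiority), normal approximation, no dropout, and true equality when computing non-inferiority power. Effects are in SD units of the outcome.

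**Step 1: the plan's own figure.** 8 × 75 = 600, so the total agrees. The 75 itself cannot be reproduced without a level, an effect and an SD. Solved backwards, d = (1.960 + 0.842) × √(2/75) = 2.802 × 0.1633 = 0.458 SD for one pair. Other readings also give 75 per group at 80% power: 0.406 SD at one-sided 5%, 0.545 SD at two-sided 1.25% (four pairs), or Cohen's f = 0.156 for an overall eight-group ANOVA. The stated size therefore does not identify the hypothesis behind it.

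**Step 2: chance of a non-significant result when digital is truly worse by d.** P = 1 − [Φ(d/SE − 1.96) + Φ(−d/SE − 1.96)], with SE = √(2/n).
- n = 75, SE = 0.1633, d = 0.2: d/SE = 1.225, P = 1 − (0.231 + 0.001) = 77%.
- n = 75, d = 0.3: d/SE = 1.837, P = 1 − 0.451 = 55%.
- n = 50, an illustration of the shortfall foreseen in section 3, SE = 0.2: 83% at d = 0.2 and 68% at d = 0.3.

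**Step 3: precision.** The 95% confidence interval half-width at 75 against 75 is 1.96 × 0.1633 = 0.32 SD.

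**Step 4: smallest margin with 80% non-inferiority power at true equality.** Margin = 2.802 × √(2/n).

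| Contrast | n per format | Smallest margin |
|---|---|---|
| One pair | 75 | 0.46 SD |
| Pairs II–IV pooled (3 × 75) | 225 | 0.26 SD |
| All four pairs pooled (4 × 75) | 300 | 0.23 SD |

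The pooled rows use the simple two-sample formula and full recruitment.

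**Step 5: power at 75 against 75 for a given margin.** Power = Φ(margin/0.1633 − 1.96).

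| Margin | Power | n per group for 80% |
|---|---|---|
| 0.2 SD | 23% | 393 |
| 0.25 SD | 33% | 252 |
| 0.3 SD | 45% | 175 |
| 0.4 SD | 69% | 99 |
| 0.5 SD | 87% | 63 |

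**Step 6: scale in days, illustration only.** For an assumed SD of 3, 4 or 5 days, the 0.458 SD margin is 1.4, 1.8 or 2.3 days, and the half-width in step 3 is 1.0, 1.3 or 1.6 days.

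**The case against.** The strongest reply is that this is a condensed article. Its formal goal is neutral, the claim of being no worse sits in the Discussion and as a belief in the Abstract, and the margin, decision rule and analysis sets may be in a full protocol or SAP that is not shown. Part of this stands: the absence of analysis detail is not itself a fault. It does not remove the point, because the article states an intention to demonstrate, a set of methods and a power figure, and these do not fit together. Hypothesis type and margin determine sample size, so they belong with the power statement.

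Four stronger readings are tempting, and the article does not support them.
- A reader might infer that a non-significant result will be reported as proof. No section says so; the risk is that it could be.
- A reader might infer that the trial cannot support its aim at all. A significant result in favour of digital would support it.
- A reader might infer that ANOVA is the wrong model. ANOVA or a linear model yields the confidence interval that is needed, and the list in section 2.11 is open-ended. What is missing is the margin and the rule.
- A reader might infer that poor adherence always pushes towards apparent equality. Section 3 expects lack of human contact to affect adherence in the digital format. If adherence is poor mainly there, digital would tend to look worse under intention-to-treat. Dilution arises when both formats adhere poorly.

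**Conclusion.** The point holds as a mismatch between the stated aim, the stated methods and the stated sample size. Short of superiority, the trial as written has no means of supporting a claim that digital is no worse, and non-significance could be misread as support. For a single pair of 75 against 75, a deficit of 0.2 SD would go undetected 77% of the time and one of 0.3 SD 55% of the time. That size gives 80% non-inferiority power only for a margin of about 0.46 SD or wider.

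These figures rest on the assumed two-sided 5% level, no dropout and, for the margins, true equality. Values in days depend on an SD that the article does not give. Pooling formats would allow a tighter margin, but the gain depends on full recruitment and on which pairs are pooled. The calculations do not show that any particular margin is clinically acceptable, nor that the planned number will suffice once one is chosen.

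**What to change.** Choose one of two routes before outcome data are seen.

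**Non-inferiority.**
- State the digital-versus-conventional comparison as non-inferiority on change in headache days, with a margin in days justified on clinical grounds and not by what the sample can support.
- Name one primary contrast: a specific pair or a defined pooled contrast. If pooled, say whether pair I is included. It differs only in diary format (Table 3), so if diary format has little effect, including it would dilute a real deficit.
- Define the direction of the difference. The outcome is a reduction, so a worse digital result is a smaller reduction; the sign is the opposite of that for a count of days.
- Declare non-inferiority only if the 95% confidence limit of the model-based difference excludes the margin in both the intention-to-treat and per-protocol sets.
- In section 2.3, state the margin and the power that the planned size delivers, and the power at the smaller size that section 3 foresees.

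**Difference.** Reword the aim as testing for a difference, report the difference with its confidence interval, and state that non-significance will not be read as showing digital to be no worse.

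Either route changes wording in sections 2.3, 2.11 and 3 and uses data already planned for collection. The cost of the first is agreeing one margin and possibly publishing a less favourable power figure. Whether more patients are needed cannot be said until the margin and SD are fixed.
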